## Methods

### Study Design

This is a prospective, randomized, sham-controlled, single-center study (Registration number: ChiCTR210049828) that will be conducted in the Department of Neurorehabilitation, Wuxi Tongren Rehabilitation Hospital, China. Hospitalized patients with chronic post-stroke aphasia are recruited to participate in the study. They are randomly assigned with a ratio of 1:1 to a real or sham stimulation group. Details about the study design and data collection are shown in Figure 1 and Table 1. On the day of enrollment (T0), after the end of cerebellar cTBS intervention (T1), and 12 weeks post-treatment completion (T2), aphasia test batteries and speech acoustic analyses are performed to evaluate language functions in post-stroke aphasia. Also, RS-fMRI data are collected before and after the end of the intervention. This study has been approved by the Ethics Committee of Wuxi Mental Health Center and Wuxi Tongren Rehabilitation Hospital (WXMHCIRB2021LLky078).

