### Sample Size

The sample size was calculated using PASS software (v.15.0) on the basis of previous studies. With an effect size of 0.5 based on the WAB-AQ (Hu et al., 2018), we expect that the target effect size had 80% of power with a type I error of 5% (α = 0.05). Thus, the sample size of each group is at least 16. With an assumption of 20% dropout rate, a sample size of 20 participants will be targeted for each group.

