### Data Analysis

Repeated-measures analysis of variances (RM-ANOVAs) are performed to examine differences in the WAB, BDAE, and BNT scores as well as speech parameters across the conditions, with a within-subject factor of phase (pre- vs. post-treatment) and a between-subject factor of group (real vs. sham cTBS). In the *post hoc* analysis, multiple comparisons are corrected with Bonferroni adjustment. Prior to entering the data into the RM-ANOVAs, Kolmogorov–Smirnov test is used to verify whether they are normally distributed. For non-normally distributed measures, the Wilcoxon Signed Rank Test is used for comparison across the conditions. The intention-to-treat (ITT) analysis is used when there are missing data.

The preprocessing of RS-fMRI data is conducted using DPABI software (v. 6.1) on the MATLAB platform (Mathworks, Natick, MA, United States) (Yan et al., 2016). The main steps are as follows: (1) use MRIConvert software (v. 2.1.0, Lewis Center, Eugene, OR, United States) to convert raw data in DICOM format to NIFI format; (2) remove the first 10 slices and correct the remaining 230 slices for slice timing; (3) correct head motion exceeding 3 mm in any direction or head rotation exceeding 3°; (4) spatially normalize the functional images to a standard Montreal Neurological Institute (MNI) space and resample them to a voxel size of 3 mm × 3 mm × 3 mm; (5) apply a band-pass filter (0.01–0.08) for each voxel to reduce the influence of low frequency fluctuation and high-frequency noise (Lv et al., 2018); and (6) smooth the functional data with a 6-mm full width at half maximum (FWHM) Gaussian kernel.

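### Intention-to-treat is invoked only when data are missing, while the named tests need complete records and no method for incomplete data is named

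*Protocol article*

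**What the plan says.** All of the following is in the protocol article.

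- **Data Analysis, ITT.** One sentence, the only mention in the article: "The intention-to-treat (ITT) analysis is used when there are missing data".
- **Data Analysis, model.** "Repeated-measures analysis of variances (RM-ANOVAs) are performed to examine differences in the WAB, BDAE, and BNT scores" and the speech parameters, "with a within-subject factor of phase (pre- vs. post-treatment) and a between-subject factor of group (real vs. sham cTBS".
- **Data Analysis, fallback.** "For non-normally distributed measures, the Wilcoxon Signed Rank Test is used for comparison across the conditions".
- **Sample Size.** At least 16 per group are required, and then: "With an assumption of 20% dropout rate, a sample size of 20 participants will be targeted for each group". The article does not say at which visit the losses are expected.
- **Study Design and Table 1.** Language outcomes are measured at enrolment (T0), "after the end of cerebellar cTBS intervention (T1), and 12 weeks post-treatment completion (T2".

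The article names no imputation rule and no likelihood-based method. It also does not say that incomplete patients are deleted.

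**The concern.** ITT is a rule about the analysis set: every randomised patient counts, in the arm to which chance assigned them. It is not a technique for missing values and cannot be switched on by their presence. As written, the sentence does two things badly. It makes a principle that should be unconditional depend on something learned during the trial. It also reads as if naming ITT settled the handling of missing data, which it does not.

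The tests around it make this matter. Both work on complete records, and one patient in five is expected to be lost. If nothing further is applied, the result would be an analysis of patients with complete data under an ITT label. Such an analysis is open to bias if the reason for leaving is related to how the patient is doing, and it discards measurements already taken.

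**Working it through.** **Inputs.** From Sample Size: 16 per group before dropout, 20% dropout, 20 per group targeted, "With an effect size of 0.5 based on the WAB-AQ", "80% of power with a type I error of 5% (α = 0.05". From Study Design: 1:1 allocation and visits T0, T1 and T2. Assumed here, because the article does not give them: two-sided testing, a pre-post correlation of 0.7, and the pattern of dropout.

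**1. The plan's own figure.** 16 / (1 − 0.20) = 20 per group, 40 in all. It reproduces exactly. The plan therefore expects 40 × 0.20 = 8 losses, leaving 32 patients, 16 per arm if losses are equal.

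**2. What the named tests need.** With two phases, the group-by-phase test in a repeated-measures ANOVA is the two-sample t-test on each patient's change, post minus pre. A patient without the post value has no change score and cannot enter. The signed rank test ranks paired differences and has the same limit. Neither offers a way to keep an incomplete patient.

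**3. How many patients this touches.** Let k of the 8 losses occur before T1 and the rest between T1 and T2. With no method for incomplete data:

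| Analysis | Patients used | Range |
|---|---|---|
| T0–T1, two phases as written | 40 − k | 32 to 40 |
| Any comparison that needs T2 | 32 | 32 |
| T0, T1 and T2 as three phases, if that is intended | 32 | 32 |

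So 8 is an upper limit for the two-phase T0–T1 model, reached only if every loss falls before T1.

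**4. Possible bias (illustration).** No true effect; T0–T1 correlation 0.7, so the SD of change is √(2 × (1 − 0.7)) = 0.775 baseline SD; 4 of 20 lost per arm; t-test on change in those remaining; 4,000 simulated trials per case.

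- Loss at random in both arms: mean estimate −0.002 SD, type I error 5.2%.
- Loss at random in the sham arm, but all four real-arm losses from the poorer-responding half: mean estimate 0.145 SD, type I error 7.4%.

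Hand check of the second case: the lower half of a normal distribution averages 0.798 SD below the mean, so removing 4 such patients of 20 shifts the remaining mean by about 4 × 0.798 × 0.775 / 16 = 0.155. The simulated value is slightly lower, as expected in samples of 20. Against a standard error of 0.775 × √(2/16) = 0.274, the bias is about half a standard error.

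A milder case, which supposes an analysis at T2: 17% missing T2, with loss depending on the T1 change, correlation 0.8 and a true effect of 0.500. The completers' mean estimate was 0.471, against 0.493 by likelihood.

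**5. Power against the plan.** The plan sizes the trial for 16 per arm. With n = 2(1.960 + 0.842)² / d², 16 per group (15.7 rounded up) corresponds to d = 1.0; d = 0.5 would need 63. The article does not say which kind of effect size its 0.5 is, so d = 1.0 is an assumption. At d = 1.0, normal approximation:

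- 16 per arm: Φ(√8 − 1.960) = Φ(0.868) = 0.807
- 20 per arm: Φ(√10 − 1.960) = Φ(1.202) = 0.885

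The t distribution gives 0.781 and 0.869. At d = 0.5 it gives 0.278 and 0.338. The 16-per-arm line is the planned case; the 20-per-arm line assumes that nobody drops out.

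**The case against.** The strongest reply is that this is one loosely worded sentence in a condensed article. Its natural meaning may be that incomplete patients are kept, by a rule held in a full protocol or analysis plan that is not shown. That largely stands. It rules out treating the absence of a method as a fault in itself. It does not rescue the sentence: a fuller document could supply a method, but would still have to correct what the article says ITT is, and a method that uses incomplete records must be joined to tests that cannot use them unaided.

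Four stronger readings are tempting, and the documents do not support them.

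- **That the plan performs a completers analysis and calls it ITT.** Deletion of incomplete patients is inferred from the tests; the article neither states nor excludes it.
- **That every patient with a missing visit is lost.** Phase is written as pre versus post. A patient who lacks only T2 stays in a T0–T1 model.
- **That with complete data the plan abandons the randomised arms.** The group factor is real versus sham, and Study Design defines the groups by random assignment. No as-treated or per-protocol set is mentioned.
- **That dropout cuts power from 87% to 78%.** This compares the planned 16 per arm with a trial without dropout, which the plan never assumed, and it rests on d = 1.0.

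**Conclusion.** The point holds in a limited form. The Data Analysis section treats ITT as a remedy for missing data, conditional on their occurrence, and sets it beside tests that need complete pairs without naming a method that could reconcile the two.

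If no such method is used, up to 8 of 40 randomised patients would leave an analysis labelled ITT. This figure rests on the planned 20% dropout; for T0–T1 the number lies anywhere from 0 to 8. The consequence is lost information and possible bias. The bias ranges from nil under random loss to about 0.14 baseline SD, with type I error near 7%, under a deliberately selective pattern in one arm. These are illustrations under assumed correlations and dropout patterns, not forecasts. There is no power shortfall against the plan, because 16 per arm was already budgeted for.

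The sentence should be corrected before analysis. The point does not call the design or the sample size into question.

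**What to change.** Replace the sentence with text to this effect:

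*All randomised participants are analysed in their allocated arm in every efficacy analysis, whether or not data are missing. WAB-AQ is analysed with a likelihood-based linear mixed model over T0, T1 and T2, with baseline as an outcome and a baseline mean common to both arms, using all available measurements and assuming that data are missing at random. One sensitivity analysis examines departures from that assumption.*

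Multiple imputation is an acceptable alternative. Baseline should be an outcome rather than only a covariate: a model of T1 and T2 with baseline as covariate omits patients who have no later value, and so would not meet its own commitment to include everyone. Where the rank-based fallback is used, say how incomplete pairs are handled.

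**Cost.** New wording and a little more analysis work; no change to sample size, visits or treatment. Two limits should be stated openly. Patients with no post-baseline visit add little information on the treatment effect, so the power of a full 20 per arm is not recovered. And the mixed model does not remove bias when loss depends on values never observed, as in the selective case above, which is why the sensitivity analysis is needed.

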### Outcome Measures

The primary outcome measure is the WAB assessment that is divided into four subitems including spontaneous speech, auditory verbal comprehension, repetition, and naming. The original scores of the four items are 20, 200, 100, and 100, respectively. An aphasia quotient (AQ) is calculated using the following formula: AQ = (spontaneous speech + auditory verbal comprehension/20 + repetition/10 + naming/10) × 2. The AQ indicates the severity of aphasia and can be used as an index for evaluating the improvement and deterioration of aphasia. The highest AQ score is 100, and the normal range is 98.4–99.6. AQ <93.8 is considered as aphasia.

In addition to the WAB scores, there are several secondary measures of treatment outcome including BDAE, Boston Naming Test (BNT), speech acoustic parameters, and RS-fMRI. BDAE is used to measure the severity of impaired language function that can be divided into five grades from severe to mild. The BNT is an assessment tool to measure the confrontational word naming of 30 object pictures. The speech acoustic parameters include fundamental frequency, intensity, speaking rate, maximum phonation time, range of voice features, and speech intelligibility. Speech signals are recorded using a laptop at sampling frequency 44.1 K Hz and Praat software is used to extract acoustic parameters.

RS-fMRI data are acquired using a 3.0 T MAGNETOM Skyra scanner (Siemens, Germany). The participants are instructed to lie still with their eyes closed and think of nothing. Functional images are obtained using echo-planar imaging (EPI) pulse sequence with the following parameters: repetition time (TR) = 2,000 ms; echo time (TE) = 30 ms; 35 slices, field of view (FOV) = 224 mm × 224 mm; slice thickness = 3.5 mm; layer spacing 0.7 mm; flip angle (FA) = 90°; acquisition matrix 64 × 64; voxel size = 3.5 mm × 3.5 mm × 3.5 mm. For registration purposes, a set of high-resolution structural images are acquired through a T1-weighted sequence: 192 sagittal slices; slice thickness = 1 mm; TR = 6.6 ms; TE = 3.1 ms; FA = 12°; FOV = 256 mm × 256 mm. The scanning lasted for 8 min and produced 240 brain volumes.

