After the preprocessing, regional homogeneity (ReHo), degree centrality (DC), and seed-to-voxel analyses are conducted to measure the local and global functional connectivity within the language networks. ReHo is calculated based on the Kendall’s coefficient of concordance (KCC), which measures the consistency of the time signal between a voxel and surrounding voxels. Higher ReHo values represent better consistency between the local voxel and the regional brain activities. DC values reflect the network connection intensity between a certain voxel and all of the brain, indicating the importance of this voxel as the network node (Zang et al., 2004). One-way ANOVAs are conducted on the ReHo and DC values to explore differences across the conditions within the predefined gray matter mask. The ANOVA F maps are corrected using Gaussian random field (GRF) correction (single voxel *p* < 0.001, cluster level *p* < 0.05). The ReHo and DC values of the peak voxels in the surviving clusters are extracted and entered into SPSS (v. 22) for further analysis. Seed-to-voxel analyses are conducted with *a priori* regions of interest (ROI). The ROIs consist of language-related regions in cerebellar Crus I; IFG pars opercularis; IFG pars triangularis; primary motor cortex (M1); anterior and posterior STG; angular gyrus; anterior and posterior supramarginal gyrus (SMG), which are selected from the AAL atlas (Tzourio-Mazoyer et al., 2002). These ROI-based functional connectivity maps are statistically compared between pre- and post-treatment and between real cTBS and sham stimulation group. Differences across the conditions are considered significant when *p* < 0.05 at the voxel level, with a false discovery rate (FDR) cluster corrected *p* < 0.05.

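### Computing ReHo after 6-mm smoothing builds neighbour concordance into the measure and lowers its sensitivity to treatment-related change

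*Protocol article*

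**What the plan says.** Under Data Analysis, the protocol article numbers six RS-fMRI preprocessing steps. Step 4 normalises the images and is to "resample them to a voxel size of 3 mm × 3 mm × 3 mm". Step 5 is to "apply a band-pass filter (0.01–0.08) for each voxel". Step 6, the last, is to "smooth the functional data with a 6-mm full width at half maximum (FWHM) Gaussian kernel".

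The next paragraph sets the order of what follows: "After the preprocessing, regional homogeneity (ReHo), degree centrality (DC), and seed-to-voxel analyses are conducted". It bases ReHo on Kendall's coefficient of concordance, "which measures the consistency of the time signal between a voxel and surrounding voxels". On inference it says: "One-way ANOVAs are conducted on the ReHo and DC values to explore differences across the conditions within the predefined gray matter mask". The F maps are GRF-corrected, and peak-voxel values from surviving clusters go on to further analysis.

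No unsmoothed branch is described for ReHo, and no smoothing of finished ReHo maps. As written, ReHo is calculated on smoothed time series.

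**The concern.** Smoothing replaces each voxel's time series with a weighted average of its own and its neighbours' series. ReHo then asks how well those same neighbours agree. Part of the agreement has been put there by the processing, whether or not there is any neural synchrony.

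This adds a floor to ReHo and leaves less room for differences in true local synchrony to show. RS-fMRI is a named secondary outcome and is the trial's evidence on mechanism. ReHo is tested voxel by voxel at p < 0.001 with about 20 patients per arm. If sensitivity is lost for an avoidable reason, a null ReHo result cannot be read clearly: it could mean no change in local synchrony, or a change that the processing hid.

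**Working it through.** The article gives no ReHo value, variance or power figure, so there is no ReHo result to reproduce. Its scan figures agree with each other: 240 volumes × 2 s = 480 s = 8 min, and 240 − 10 = 230 time points (reading the word slices in step 2 as volumes).

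**Inputs from the article.** Kernel FWHM 6 mm; voxel 3 mm; "repetition time (TR) = 2,000 ms"; 230 time points; filter 0.01–0.08.

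**Assumptions.** Filter in Hz (no unit is printed); neighbourhood of 7, 19 or 27 voxels (no size is given); white noise before smoothing.

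1. *Kernel width.* σ = 6/2.3548 = 2.548 mm, or 2.548/3 = 0.849 voxel.

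2. *Correlation induced in independent noise at distance d.* r(d) = exp(−d²/(4σ²)). With d in voxels and FWHM of 2 voxels this is 2^(−d²/2).
   - Face neighbour, d = 1: 0.71
   - Edge neighbour, d = √2: 0.50
   - Corner neighbour, d = √3: 0.35

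3. *From correlation to ReHo.* Kendall's W is the mean of the full rank-correlation matrix, diagonal included. For a 3×3×3 block the kernel correlation separates by axis. Along one axis the mean over three voxels is (3 × 1 + 4 × 0.7071 + 2 × 0.25)/9 = 6.328/9 = 0.703. In three dimensions this is 0.703³ ≈ 0.35. Without smoothing only the diagonal contributes: 1/27 ≈ 0.04.

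4. *Simulation of pure noise* (20×20×20 grid, 230 volumes, TR 2 s, 0.01–0.08 Hz):

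| Neighbourhood | Unsmoothed | Smoothed 6 mm |
|---|---|---|
| 27 voxels | 0.04 | 0.34 |
| 19 voxels | 0.05 | 0.41 |
| 7 voxels | 0.14 | 0.58 |

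The 27-voxel simulation agrees with the closed form. The conclusion does not depend on neighbourhood size.

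5. *Sensitivity with spatially limited signal* (27 voxels; signal of assumed smoothness plus white noise; amplitude doubled from 0.5 to 1.0). Entries are mean ReHo with between-voxel SD in brackets; change is divided by the pooled SD, √((SD₁² + SD₂²)/2):

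| Signal smoothness | Unsmoothed | Change/SD | Smoothed | Change/SD |
|---|---|---|---|---|
| 6 mm | 0.083 (0.012) to 0.159 (0.024) | 0.076/0.019 = 4.0 | 0.466 (0.042) to 0.490 (0.045) | 0.024/0.044 = 0.6 |
| 12 mm | 0.139 (0.017) to 0.289 (0.036) | 0.150/0.028 = 5.3 | 0.660 (0.038) to 0.709 (0.039) | 0.049/0.039 = 1.3 |

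The change shrinks and the spread does not shrink with it. Across all simulated signal settings (6 to 12 mm, amplitude 0.5 to 1.4) smoothed ReHo ran from 0.47 to 0.76. The kernel-only level of 0.34 corresponds to 0.34/0.76 = 45% up to 0.343/0.466 = 74% of those values. These rows show direction and mechanism. The SDs are between voxels in a simulation, not between patients, and each setting is a single random field.

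**The case against.** Five points can be made on the other side.

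- **The article only lists main steps.** A fuller pipeline might take ReHo from unsmoothed data. But the order is stated outright, so this is more than an omitted detail. If practice differs, the text needs correcting.

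- **The white-noise baseline is too favourable to the unsmoothed order.** Images acquired at 3.5 mm are normalised and resampled to 3 mm, and interpolation already correlates neighbours. This stands: the real unsmoothed floor would be somewhat above 0.04.

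- **Stronger readings of the size fail.** With one signal shared by the whole grid plus white noise, ReHo moves from 0.13 to 0.52 unsmoothed and from 0.82 to 0.98 smoothed as shared correlation rises from 0.1 to 0.5. A reader might infer that ReHo is pushed to its ceiling of 1 everywhere, or that 60% of sensitivity is lost (range 0.16 against 0.39). Neither follows. Values near 1 arise because smoothing averages out noise around a grid-wide signal; local-signal models give about 0.43 to 0.76. Range alone is not sensitivity: with spread counted, a rerun of that same model gives about 10.0 against 6.9 SD (loss near 30%), and about 5.7 against 5.1 SD (near 10%) for 0.1 to 0.3. A 6-mm local signal in the same rerun gives about 5.5 against 1.6 SD. The loss is model-dependent.

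- **Degree centrality is a different case.** A reader might infer that DC is materially inflated too. The article defines DC against the whole brain. By the formula above, kernel correlation reaches 0.25 for only 6 + 12 + 8 + 6 = 32 surrounding voxels. In a mask of 10,000 voxels (an assumption) that is 32/10,000, about 0.3% of possible connections. No material effect on DC is shown.

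- **The consequence is limited.** The kernel is common to both arms and both scans, so a reader who infers bias in real versus sham goes too far. ReHo is one exploratory imaging measure among the secondary outcomes. This stands.

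**Conclusion.** The point holds for ReHo. The stated order makes the kernel impose part of the concordance that ReHo is defined to measure: about 0.34 in pure noise against about 0.04 unsmoothed, for 27 voxels and white noise. A substantial part of measured ReHo then reflects processing, and every model tried shows reduced sensitivity to change in local synchrony. The true loss is unknown, because the document gives neither signal smoothness nor between-patient ReHo variance. The effect is attenuation without bias. The WAB outcome and the seed-to-voxel analysis are not affected. It is worth correcting because the fault is avoidable and bears on how a null ReHo result would be read.

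**What to change.** In Data Analysis, give ReHo its own branch: compute it on the normalised, band-pass-filtered, unsmoothed data (after step 5), then smooth the resulting ReHo maps with the same 6-mm FWHM kernel before the ANOVAs and GRF correction. Smoothing the maps retains spatial smoothness for the GRF step. Keep step 6 as it is before the seed-to-voxel analysis. State the ReHo neighbourhood size in the same sentence.

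The cost is reordering one processing step. No scans, patients or design changes are needed. If the working pipeline already runs this way, one corrected sentence is enough.

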**Methods:**

In this randomized, sham-controlled clinical trial, patients (*n* = 40) with chronic post-stroke aphasia received 10 sessions of real cTBS (*n* = 20) or sham cTBS (*n* = 20) over the right cerebellar Crus I+ a 30-min speech-language therapy. The Western Aphasia Battery (WAB) serves as the primary measure of the treatment outcome. The secondary outcome measures include the Boston Diagnostic Aphasia Examination, Boston Naming Test and speech acoustic parameters. Resting-state fMRI data were also obtained to examine treatment-induced changes in functional connectivity of the cerebro-cerebellar network. These outcome measures are assessed before, immediately after, and 12 weeks after cerebellar cTBS intervention.

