To this end, the purpose of the present study is to investigate the short- and long-term effectiveness of cTBS over the right cerebellum in augmenting language recovery in chronic post-stroke aphasia in a randomized, sham-controlled design. In addition to aphasia test batteries and speech acoustic analyses for evaluation of treatment outcome, the resting-state functional magnetic resonance (RS-fMRI) is also used to explore the neural mechanisms underlying aphasia rehabilitation. The previous studies have shown associations between improved spelling or phonemic fluency and increased resting-state functional connectivity between the cerebellum and language-related cortical regions for patients with chronic post-stroke aphasia or healthy individuals following tDCS over the right cerebellum (Sebastian et al., 2016; Turkeltaub et al., 2016). Accordingly, we hypothesize that, following cTBS over the right cerebellum, patients with chronic post-stroke aphasia will exhibit improved language functions and increased functional connectivity within the cerebro-cerebellar language network. This randomized, sham-controlled study provides significant new insights into the therapeutic efficacy of cTBS over the right cerebellum to augment SLT for post-stroke aphasia and the underlying neuroplastic mechanisms.

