## Discussion

This randomized, sham-controlled clinical trial investigates the neural and behavioral effects of cTBS over the right cerebellum on chronic post-stroke aphasia. We hypothesize that stimulating the right cerebellum with inhibitory cTBS can produce beneficial effects in augmenting SLT for language recovery in post-stroke aphasia by regulating functional connectivity between the right cerebellum and the cerebral cortical regions involved in language processing. These results can provide supportive evidence that the right cerebellum may be a potential optimal stimulation target for the treatment of chronic post-stroke aphasia.

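### The RS-fMRI analysis designates no test of the cerebro-cerebellar hypothesis, and it presents ReHo and degree centrality as language-network measures, which its own definitions do not support

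*Protocol article*

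**What the plan says.** **The imaging question**

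- Abstract, Methods: RS-fMRI is obtained "to examine treatment-induced changes in functional connectivity of the cerebro-cerebellar network".
- Introduction, final paragraph: the hypothesis is "improved language functions and increased functional connectivity within the cerebro-cerebellar language network". It gives a direction and a network.
- Discussion, first paragraph: the mechanism is narrower, namely "regulating functional connectivity between the right cerebellum and the cerebral cortical regions involved in language processing". This version has no direction.
- Outcome Measures: RS-fMRI is one of several secondary measures, listed as a modality with no variable named.

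**The imaging analysis (Data Analysis)**

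- ReHo, DC and seed-to-voxel analyses are introduced together, "to measure the local and global functional connectivity within the language networks".
- ReHo is described as the consistency of the signal in a voxel with that of its neighbours. For DC, "DC values reflect the network connection intensity between a certain voxel and all of the brain".
- ReHo and DC are compared by one-way ANOVA "to explore differences across the conditions within the predefined gray matter mask", with GRF correction (voxel p < 0.001, cluster p < 0.05).
- Seed maps start from nine region types: Crus I and eight cortical regions. They are compared before against after treatment and real against sham, at voxel p < 0.05 with FDR cluster correction at 0.05.
- The side of the Crus I seed is not given, although Interventions places the stimulation over right Crus I.

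**The concern.** The question and the analysis do not quite meet, in two ways.

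First, the sentence introducing the three metrics gives them all a scope that the following definitions do not bear out for two of them.

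Second, the hypothesis is specific (a network, a direction and, in the Discussion, a pathway), but nothing in Data Analysis says which map, seed or comparison decides it. With several metrics, nine seed types and two kinds of comparison of equal standing, the reader of the results cannot tell which finding was meant to be the evidence. The Conclusion makes the neural mechanism one of the trial's two aims, so it matters what would count as support for it.

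**Working it through.** The documents give no imaging sample size, power or overall error rate, so there is no stated figure to reproduce. The check is a comparison of texts, a count, and one illustrative calculation.

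**Step 1. Does each metric measure the hypothesised quantity?**

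| Analysis | What it relates, by the article's description | Cerebellum-cortex coupling? | Search region |
|---|---|---|---|
| ReHo | a voxel and its neighbours | no | gray matter mask |
| DC | a voxel and the whole brain | included in the total, not isolated | gray matter mask |
| Seed map, Crus I | cerebellar seed and every voxel | yes, directly | voxelwise |
| Seed maps, eight cortical regions | cortical seed and every voxel | yes, where the cluster is cerebellar | voxelwise |

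The mask is not described as limited to language regions. Even if it were, DC would still reflect connections with the whole brain.

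**Step 2. Is one comparison tied to the hypothesis?**

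No metric or seed is given precedence. For the seed maps, two comparisons are named: before against after, and real against sham. Neither alone is the between-arm difference in change. A before-after change also carries the effect of the speech-language therapy that both arms receive, and a difference between arms after treatment also carries any baseline difference. The behavioural scores have phase and group factors in a repeated-measures ANOVA; the text does not say that the maps are handled the same way.

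**Step 3. Count of maps.**

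- Seed types: Crus I, IFG pars opercularis, IFG pars triangularis, M1, anterior STG, posterior STG, angular gyrus, anterior SMG, posterior SMG = 9 (1 cerebellar, 8 cortical).
- Map families: ReHo + DC + 9 seed types = 11.
- If each seed map is compared in both ways: 2 + 9 × 2 = 20 tests.

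**Step 4. Illustration of the lack of a named test.**

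Assume that there is no true effect, that each test has a 5% chance of at least one false cluster after its own correction, and that tests are independent. The chance of at least one false cluster in m tests is 1 − 0.95^m.

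- m = 1: 5.0%
- m = 9 (seeds only): 1 − 0.95^9 = 37.0%
- m = 11: 1 − 0.95^11 = 43.1%
- m = 20: 1 − 0.95^20 = 64.2%

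The maps come from the same scans and are correlated, so these are upper-end values.

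**The case against.** The strongest case on the other side has four parts.

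**The pathway is already analysed.** Crus I heads the list of a priori seeds, and a cortical-seed map can also show a cerebellar target. A reader might infer that ReHo, DC and cortical seeds have displaced the hypothesised endpoint, or that only one map in 11 bears on it. The documents support neither: all nine seed types can show cerebellum-cortex coupling, and only ReHo and DC cannot test it. This objection stands.

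**The framing is wider than one pathway.** Only the Discussion's opening paragraph speaks strictly of right cerebellum with cortical regions. The Abstract and Introduction speak of a network, which can include links between cortical nodes. The Discussion also cites a study in healthy individuals that found changes within a left-lateralised network after cerebellar stimulation. The cortical seeds therefore follow from the stated rationale. This stands too.

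**Nobody says that any cluster would do.** A reader might infer that a cluster anywhere could be reported as the hypothesised effect. No sentence says so, and the Introduction fixes a network and a direction that such a cluster would have to match. A reader might also infer from the voxel threshold of 0.001 that the pathway is tested with low power. That threshold belongs to ReHo and DC; the seed maps use another rule, for which no power can be derived from the documents.

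**Imaging is secondary and called exploratory, and this is a condensed article.** The Abstract and Introduction describe the imaging as exploring mechanisms, and ranking secondary contrasts is often left to a fuller document. This lowers the weight of the point but does not remove it. The mismatch between the stated scope and the definitions is on the page, and a directional hypothesis is stated without any analysis being marked as its test.

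**Conclusion.** The point holds in a limited form. By the article's own definitions, ReHo cannot measure the hypothesised coupling and DC does not isolate it, and neither is shown to be confined to the language networks. The seed analysis can measure the coupling, but no seed, side or between-arm change contrast is designated as the test of the hypothesis, and correction is stated only within maps.

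The size is illustrative: up to 43% for at least one false cluster over 11 map families, or 64% over 20 tests, against 5% for one named test. These figures assume independence and a true 5% rate per test. They are not the probability of a false claim about mechanism, which would also need the right network and direction.

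Severity is minor. The primary outcome is untouched, and the change is worth making because it is cheap.

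**What to change.** In Data Analysis:

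1. Name one test of the hypothesis in the Introduction and Discussion: connectivity of the right Crus I seed with the cortical language regions already listed, compared between real and sham on the change from T0 to T1. How the regions are combined or corrected can be left to the trial team, provided that it is fixed in advance; a single average over all regions is not required.
2. Label ReHo, DC and the remaining seed maps as exploratory.
3. For ReHo and DC, either restrict the mask to the listed language regions or drop the statement that they measure connectivity within those networks. If the mask is restricted, still say that DC reflects connections with the whole brain.

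The cost is wording and, at most, one extra extraction from scans that Table 1 already schedules at T0 and T1. No patients or procedures are added. The downside is that effects outside the named contrast become exploratory.
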